## Abstract

**Background:**

Attempts to reduce high utilisation of psychiatric inpatient care by targeting the critical time of hospital discharge have been rare.

**Methods:**

This paper presents design and methods of the study "Effectiveness and Cost-Effectiveness of Needs-Oriented Discharge Planning and Monitoring for High Utilisers of Psychiatric Services" (NODPAM), a multicentre RCT conducted in five psychiatric hospitals in Germany. Inclusion criteria are receipt of inpatient psychiatric care, adult age, diagnosis of schizophrenia or affective disorder, defined high utilisation of psychiatric care during two years prior to the current admission, and given informed consent. Consecutive recruitment started in April 2006. Since then, during a period of 18 months, comprehensive outcome data of 490 participants is being collected at baseline and during three follow-up measurement points.

The manualised intervention applies principles of needs-led care and focuses on the inpatient-outpatient transition. A trained intervention worker provides two intervention sessions: (a) Discharge planning: Just before discharge with the patient and responsible clinician at the inpatient service; (b) Monitoring: Three months after discharge with the patient and outpatient clinician. A written treatment plan is signed by all participants after each session.

Primary endpoints are whether participants in the intervention group will show fewer hospital days and readmissions to hospital. Secondary endpoints are better compliance with aftercare, better clinical outcome and quality of life, as well as cost-effectiveness and cost-utility.

**Discussion:**

If a needs-oriented discharge planning and monitoring proves to be successful in this RCT, a tool will be at hand to improve patient outcome and reduce costs via harmonising fragmented mental health service provision.

**Trial Registration:**

ISRCTN59603527

## Background

Large numbers of psychic patients do not receive aftercare in the community during the period immediately following hospital discharge. The average rate of utilisation of aftercare is about 50%, with a wide range between 22 and 90% depending on the definition of aftercare [1-3]. More specifically, one third to one half of patients with schizophrenia and related disorders miss their first scheduled outpatient appointment after discharge [4]. In addition, for those who receive follow-up, the delay between discharge and receipt of aftercare (operationalised as first outpatient visit) has been found to be substantial [1,5]. Thus, limited continuity of service provision is pervasive, and time lags arising in this process have been found to increase the probability of relapse and to negatively affect patients' quality of life [1].

There have been some research efforts aimed at identifying the causes for this failure to utilise psychiatric services (for an overview see [2]). Results based on patient variables have been mostly negative, while service system variables, e.g. availability of discharge planning, have been found to facilitate access to aftercare. There is some evidence suggesting that patients who receive discharge planning are more likely to utilise outpatient mental health services and are less prone to become socially isolated and require rehospitalisation. Thus, in a sample of N = 104 inpatients with schizophrenia or schizoaffective disorder, Olfson et al. [6] found that those who had received discharge planning showed significantly better aftercare compliance (98.1 vs. 62.7%), fewer rehospitalisations (40% reduction), and better clinical outcome (34.5 vs. 41.0 BPRS-points, ES = .57) at three-month follow-up. Furthermore, in a sample of 229 inpatients with a primary psychiatric diagnosis, Boyer et al. [1] found that patients were significantly more likely to keep their initial outpatient appointment if they were involved in the outpatient programme before discharge (OR = 2.14 – 3.89) or if the discharge plan was discussed between inpatient staff and outpatient clinicians (OR = 3.17).

It appears that rather simple measures – such as timely face-to-face contact of the inpatient with the follow-up outpatient therapist(s) and/or smooth transition between in- and outpatient treatment – are likely to bring about an increase in successful community tenure. Also a time-limited critical time intervention [6,7] has been shown to yield clinical improvement. The impact of extensive strategies such as case management or the introduction of discharge coordinators, on the other hand, has been limited or controversial.

Nonetheless, the use of bridging strategies in routine practice is idiosyncratic at best. Boyer et al. [1] showed that while discussions between in- and outpatient teams regarding the arrangement of aftercare occur rather frequently (in two thirds of the cases), patient involvement with outpatient programmes while they are still in hospital is less common.

Since the 1980s considerable research effort has been devoted to high utilisation (HU) of psychiatric services. According to Hadley et al. [8], "the concept of 'heavy use' typically applies to those persons whose frequency of admission or duration of inpatient service is substantially beyond that of the majority of persons receiving similar treatment" (p. 280). Two extensive literature reviews on the topic (Kent et al. [9]: 200 publications identified, 72 described; Roick et al. [10]: 250 publications identified, 105 described) showed that overall, 10 – 30% of psychiatric patients are identified as high utilisers who consume between 50 and 80% of service resources.

Probably due to large differences between psychiatric service systems, there is no consensus on what constitutes HU. In operationalising HU, most authors solely relied on an arbitrary number of readmissions during a given time period – usually study duration. An analysis of nine studies pertaining to psychiatric inpatient treatment (cf. table 1 in Kent et al. [9]) showed that a mean number of 3.25 (SD = 1.75) admissions during 2.38 (SD = 1.51) years, i.e. 1.37 admissions per year, was used as the criterion for HU. This corresponds to Roick et al. [10] who found that overall, patients with 1 – 3 inpatient stays during one year are identified as a high utilisers. This measure is easily accessible, but has also been criticised (e.g. [11]) since patients with multiple short hospital stays might be wrongly included (since they do not use excessive resources), and patients with few very long hospital stays might be wrongly excluded, especially when observation time is short. Thus, some authors used cumulated length of stay (LOS) during a given period (in addition to or instead of number of readmissions) to identify HU. E.g. Lucas et al. [12] developed a "heaviness of use" score by combining the frequency of admissions with the total number of bed days. Exceptionally, direct treatment costs beyond cumulated inpatient costs including costs for non-inpatient care (day hospital treatment, outpatient and complementary care) was applied [13], but data collection is laborious and might not be worthwhile since costs for inpatient care make up the largest share (75–92% [9,14]) of total treatment costs.

**Table 1 T1:** Study instruments by raters and measurement points.

	*T0*	*T1*	*T2*	*T3*
*Research worker*	CAN-EU	CAN-EU	CAN-EU	CAN-EU
	CSSRI-EU	CSSRI-EU	CSSRI-EU	CSSRI-EU
	BPRS	BPRS	BPRS	BPRS
	HAM-D	HAM-D	HAM-D	HAM-D
	MANSA	MANSA	MANSA	MANSA
	EQ-5D	EQ-5D	EQ-5D	EQ-5D
*Clinician*	GAF	GAF		
	CGI	CGI		
	STAR-C	STAR-C		
		ZUF-THERA		
		DP satisfaction		
*Patient*	SCL-90-R	SCL-90-R	SCL-90-R	SCL-90-R
	STAR-P	STAR-P	STAR-P	STAR-P
		ZUF-8		
		DP satisfaction		

*Notes*: DP = Discharge Planning. See text for other abbreviations.

### Objectives and purpose of the study

Objective of the study is to test the following hypotheses.

#### Primary

High utilisers of psychiatric services who receive a needs-oriented discharge planning and monitoring programme will show fewer hospital days and readmissions to hospital.

#### Secondary

Subjects receiving the intervention will show better compliance with aftercare as well as better clinical outcome and quality of life. Furthermore, the intervention will show cost-effectiveness and cost-utility, and community-based psychiatrists whose patients receive the new discharge protocol will show better compliance with treatment recommendations.

## Methods and design

A clinical trial entitled "Effectiveness and Cost-Effectiveness of Needs-Oriented Discharge Planning and Monitoring for High Utilisers of Psychiatric Services" (NODPAM) will be conducted. Coordinating centre (CC) is Ulm University's Department of Psychiatry II (Günzburg). Participating centres are the Departments of Psychiatry and Psychotherapy at the Universities of Düsseldorf, Greifswald, and Regensburg, and Ulm University's Department of Psychiatry I (Ravensburg). This paper describes design and methods of the NODPAM trial as outlined in the trial protocol which has been submitted to the funding body (German Research Foundation) on July 15, 2005 after having attended to the funders' and independent reviewers' comments on the original proposal and its revision. Before the start of recruitment in April 2006, minor changes have been applied^1^.

### Overview

NODPAM is a randomised controlled prospective trial with four measurement points during an 18-month study period (see Figure 1, upper part). Assessments will take place at baseline, three, six, and 18 months after discharge. We believe that this design is appropriate to answer the research questions since on one hand it allows to examine the short-term (three months after baseline), mid-term (six months) and long-term (18 months) effects of the intervention, and on the other hand, the burden on participants (patients and clinicians) is not too high which will help to keep low study attrition. In the event of rehospitalisation, data assessment will proceed as originally scheduled, allowing some delay in case the patient should be in an acute crisis making assessment impossible. Assessment will be carried out by a research worker (different in person from the intervention worker).

**Figure 1 F1:**
[figure not shown]
Trial design (timing and projected N for data collection and intervention).

### Randomisation

A central randomisation procedure will be conducted by an independent unit (Ulm University's Institute for Biometrics). Stratification will be applied since we will conduct a multicentre trial, and, furthermore, since the intervention might have different effects as to diagnostic criteria, gender, and chronicity. In order to ensure an adequate distribution of patients with regard to these aspects, strata will be centre (five centres), primary diagnosis (ICD-10 Chapter V codes F20 – F29 vs. F30 – F39), gender (male vs. female) and chronicity (shorter vs. equal to or longer than three years). If during recruitment a patient fulfils inclusion criteria and has given informed consent, a fax will be sent to the randomisation centre which will perform randomisation, generate a patient code, and send it back to the study centre.

Cluster randomisation (at the clinician level) will not be employed since it would severely disrupt clinical routine and might result in undesired between-centre effects. Furthermore, in many wards of the participating services, only one clinician is present. Moreover, cross-contamination among inpatient clinicians is not to be expected since the intervention is low profile, restricted to one pre-discharge session, and will be carried out by a research worker with limited clinician involvement.

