### Sample size

Power calculation for a panel study with four points of assessment was based on the approach suggested by Hedeker et al. [32]. For a high utiliser population, previous research [33] found mean number of inpatient days during 12 months after discharge to be 47 (SD = 83) days (projected mean number for 18 months = 71 days). Based on existing studies, the mean reduction of inpatient days due to the planned intervention was assumed to be 40%. A small effect size (0.2 SD) should be detected with a power of 0.80 at a two-tailed significance level of 0.05. Panel attrition was estimated 10% at each measurement point. With regard to data analysis, a constant group effect over time with a random-effect structure and auto-correlated results was expected. A baseline sample size of 242 participants in each group was calculated to be sufficient.

Accordingly, after rounding to no decimals, a total sample size of 490 participants (N = 98 at each site) will be included in the study. Participants will be randomly assigned to the intervention (N = 245, N = 49 per site) or control group (N = 245, N = 49 per site).

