### Statistical analysis

The primary endpoints will be derived from the difference in LOS and number of hospitalisations between T0 and T1, T2, and T3. The secondary endpoints will be calculated from the differences in sum (or – if applicable – subscale) scores of the secondary outcome measures between T0 and T1, T2, and T3. Multiple measurement points have been chosen in order to scrutinise the intervention's effect over time, especially the question of whether short- and mid-term effects would persist.

Analyses will start once baseline data have been collected and cleaned. Descriptives of all outcome measures will be produced, and outcome trajectories from T0 – T3 will be examined via exploratory analyses. The effect of the intervention on reduction of number of inpatient days as well as on clinical outcomes, quality of life, and compliance will be tested by means of random-effect regression models including a constant group effect across time [35-37]. Due to the application of a generalised least square (GLS) estimation weighted for the lengths of the time series for each case, these models allow the inclusion of cases with incomplete (unbalanced) data across panels. Due to expected skewness of the primary dependent variable (LOS), bootstrapping methods will be applied for the estimation of standard errors and confidence intervals. Cost-effectiveness of intervention will be tested by means of the net-benefit approach [38], and its cost-utility by using QALYs generated from EQ-5D.

Analysis will be carried out according to the principle of intention-to-treat. In case attrition should exceed the projected rate of 10%, additional per-protocol analysis will be performed.

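### The analysis models name none of the four factors used to stratify randomisation; if these are prognostic and left out, the trial gives up some precision, but not validity or planned power

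*Protocol article*

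**What the plan says.** **Randomisation** lists the factors: "strata will be centre (five centres), primary diagnosis", followed by gender and chronicity, the last split at three years. Centre is a factor because the trial is multicentre. Diagnosis, gender and chronicity are added "since the intervention might have different effects as to diagnostic criteria, gender, and chronicity". The section also gives a second aim, an adequate distribution of patients over these characteristics.

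**Statistical analysis** tests inpatient days, clinical outcomes, quality of life and compliance with random-effect regression models that include a group effect constant across time. Incomplete series are handled by weighted GLS. Because length of stay is expected to be skewed, "bootstrapping methods will be applied for the estimation of standard errors and confidence intervals". The section names no stratification factor, interaction or subgroup analysis, and does not say how bootstrap samples are drawn.

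**Sample size** rests on the same kind of model: "a constant group effect over time with a random-effect structure and auto-correlated results was expected". It mentions no covariates.

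**The concern.** Stratified allocation balances the arms on the chosen factors, so variation between strata largely drops out of the true sampling error of the group comparison. An analysis gets the benefit only if it knows about the strata. An unadjusted model leaves between-stratum variation in the residual. A bootstrap that resamples patients without regard to strata puts that variation back into the standard error. The reported error is then larger than the error the design delivers.

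The article describes the model, the estimator and the method for standard errors in some detail, and the randomisation factors appear in none of them. Followed as written, the analysis would forgo precision that the stratification has already made available. The trial aims at a 0.2 SD effect, so free precision is worth having.

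A smaller matter is that possible effect differences by diagnosis, gender and chronicity are offered as a reason to stratify, and the analysis section does not return to them.

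**Working it through.** **1. The plan's own sample size.** The Sample size section sets the target: "A small effect size (0.2 SD) should be detected with a power of 0.80 at a two-tailed significance level of 0.05". Its other inputs are a 10% loss per assessment, four assessments, and a constant group effect with autocorrelation. The correlation is not given.

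Formula: n per arm = 2(1.960 + 0.842)² × w'Rw / 0.2². Here w_t = (1/4)/√(retention_t), retention is 1, 0.9, 0.81, 0.729 (10% loss compounded, an assumption), and R is the correlation matrix.

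- Leading factor: 2 × 7.849 / 0.04 = 392.4, which is 393 per arm for a single measurement.
- With AR(1) and an assumed correlation of 0.5, w'Rw = 0.607, so n = 238.2, or 239 per arm.
- The stated 242 is matched exactly at a correlation of about 0.51 (AR(1)) or 0.37 (compound symmetry).

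So 242 is consistent with a plausible correlation, and the planned 80% is taken as the starting point below.

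**2. The strata.** 5 × 2 × 2 × 2 = 40 cells; 490/40 = 12.25 patients per cell.

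**3. Effect of leaving the strata out.** Let R² be the share of outcome variance explained by the four factors. The documents give no value, so a range is used. Let f = 1/√(1 − R²), and λ = 1.960 + 0.842 = 2.802, the standardised effect that gives 80% power when R² = 0. With allocation balanced within strata:

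- reported SE / true SE without adjustment = f
- actual alpha without adjustment = 2[1 − Φ(1.960 f)]
- power without adjustment = Φ((λ − 1.960) f)
- power with adjustment = Φ(λ f − 1.960)

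| Assumed R² | SE too wide by | Actual alpha, unadjusted | Power, unadjusted | Power, adjusted |
|---|---|---|---|---|
| 0.01 | 0.5% | 0.049 | 0.801 | 0.804 |
| 0.05 | 2.6% | 0.044 | 0.806 | 0.820 |
| 0.10 | 5.4% | 0.039 | 0.813 | 0.840 |
| 0.20 | 11.8% | 0.028 | 0.827 | 0.879 |

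Worked row, R² = 0.10: f = 1/√0.90 = 1.054. Unadjusted power is Φ(0.842 × 1.054) = Φ(0.887) = 0.813. Adjusted power is Φ(2.802 × 1.054 − 1.960) = Φ(0.993) = 0.840.

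Unadjusted power also rises with R², because balance shrinks the true error whether or not the analysis uses it. The gain from adjusting is the difference between the last two columns: 1.4, 2.7 and 5.2 percentage points at R² = 0.05, 0.10 and 0.20.

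**4. Simulation check.** 490 patients, 40 strata, blocks of 4 (assumed), 2,500 runs per setting. The ratio of unadjusted to adjusted SE was 1.00, 1.02, 1.05 and 1.11 at R² = 0, 0.05, 0.10 and 0.20. Unadjusted type I error was 0.052, 0.047, 0.039 and 0.030. Adjusted type I error stayed near 0.05. This agrees with the formulas.

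**5. Power for an interaction.** With a factor split 50/50, the SE of the interaction is twice that of the main effect. For an interaction as large as the main effect, power is Φ(2.802/2 − 1.960) = Φ(−0.559) = 0.288, about 29%. It reaches 80% only when the interaction is twice the main effect.

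**The case against.** The strongest reply is that this rests on silence in a journal article. The model is described as *including* a group effect, which does not mean that it contains nothing else. Covariate lists and bootstrap schemes are commonly left to a fuller document that is not shown. This stands as a limit: a reader might infer that the factors are excluded from the analysis, and the text does not say so. What remains is that the model as described would be improved, at no cost, by naming them.

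A reader might also infer that the trial is underpowered or that its test is invalid. Neither follows. Alpha falls below 0.05, unadjusted power does not fall below the planned 80%, and 242 per arm is not shown to be wrong.

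A third inference would be that the reason for stratifying contradicts the analysis. The documents do not support that. The effect-difference reason does not cover centre. Balance is a second stated aim, and stratified allocation meets it unaided. A group effect constant across time means constant over visits, which does not rule out differences between strata.

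Finally, the endpoints are said to derive from differences from T0, which could remove stable stratum differences and lower R². That is possible but not settled. Outcome measures describes the primary outcomes as cumulated over the study period, so the difference may simply mean days accrued. Differencing would also leave stratum differences in change untouched.

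**Conclusion.** The point holds as a modest matter of efficiency. Allocation uses four factors that the described models do not name. If the factors are prognostic and are ignored in both the model and the bootstrap, standard errors are conservative: about 5% too wide or less for R² up to 0.10, and about 12% at 0.20. The cost is at most about 5 percentage points of power over the range shown, on top of a planned 80% that stays intact.

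This rests on three assumptions that the documents do not settle: the value of R², that the strata are in fact omitted, and that allocation is closely balanced within cells of about 12 patients. The missing interaction tests are secondary, since such tests could settle little at this sample size.

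**What to change.** - State that centre, primary diagnosis, gender and chronicity enter the primary and secondary models as main effects. This adds 4 + 1 + 1 + 1 = 7 parameters.
- State that bootstrap samples are drawn as whole patients, with all their visits, within centre and arm, and that the adjusted model is refitted in each sample. Centre by arm gives 490/10 = 49 patients per cell. The full strata by arm would give only 490/80, about 6, which is thin for resampling.
- Optionally, pre-specify group-by-diagnosis, group-by-gender and group-by-chronicity interactions as exploratory, reported as estimates with confidence intervals and with a note of the roughly 29% power.

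The cost is a few sentences in the analysis section. No new data are needed, because all four factors must be known to randomise a patient. The choice should be fixed before outcomes are analysed, since the Blinding section leaves the investigators and the research worker unblinded.

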### Blinding

Due to the nature of the intervention, patients, clinicians, and intervention workers cannot be blinded to patient allocation. The natural flow of the study will also prevent the research worker from being blinded. Furthermore, blinding to patient allocation and centre affiliation of principal and responsible investigators as well as of the person performing randomisation is considered neither feasible nor necessary because no related bias is expected, and a blinded intermediate risk assessment, e.g. in order to identify excess mortality of participants as could be the case with invasive interventions or acutely critical conditions, is not required.

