### Outcome measures

Assessment will take place at baseline and three (3, 6 and 18 months) follow-up measurement points in each participating centre (see Figure 1). Patients will receive a remuneration of 30 € for each assessment. Secondary outcomes will be provided by independent raters (research workers trained in study instrument use), clinicians, and patients. See Table 1 for an overview of the instruments used.

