#### Rater perspective (T0 – T3)

Cumulated *LOS *and number of *readmissions *during the study period (primary outcomes) will be assessed by a research worker at T1 – T3 via the German version of the "Client Sociodemographic and Service Receipt Inventory" (CSSRI-EU). This is a standardised instrument for the comprehensive assessment of mental health service use and costs [16] of which a German version is available [17]. It provides detailed information on direct (e.g. hospital in-patient days, out-patient/day care attendances, community-based service contacts, medication profile) and indirect (e.g. days of work loss, state benefits, source/level of income) costs and has been used in a number of German studies^2^.

Assessment of *needs *will be carried out with the German version of the "Camberwell Assessment of Need – European Version" (CAN-EU [18]), an interviewer-administered instrument comprising 22 individual domains of need. Staff and user ratings can be obtained; we administered only the user rating. *Psychopathology *will be assessed using the "Brief Psychiatric Rating Scale" (BPRS [19]) which is a standardised instrument for the assessment of psychopathological symptoms. *Depression *will be tapped into using the "Hamilton Depression Scale" (HAM-D [20]). *Quality of life *will be measured via a) the "Manchester Short Assessment of Quality of Life" (MANSA [21]) which is a disease specific instrument for the multidimensional assessment of objective and subjective quality of life in persons with severe mental illness and b) the EuroQol group's EQ-5D, a generic quality of life assessment instrument which has been developed for the computation of quality adjusted life years (QALYs) and whose psychometric properties and applicability in persons with severe mental illness have been tested [22].

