#### Pre-discharge intervention session

The intervention worker obtains the relevant information of patients' met and unmet needs in a basic plan (results of the CAN rating) from the research worker. The first joint (pre-discharge) intervention session in general takes place seven days prior to hospital discharge with the following people participating: in-patient clinician, patient and carers if the patient wants to. There is a guided discussion of the critical domains of need identified on the basis of CAN ratings which require both current and post-discharge measures and/or interventions. The handwritten draft of the post-discharge treatment plan contains every addressed need with a precise problem definition, objectives, time-frame regarding goal attainment and persons responsible for the implementation. The treatment plan is signed by all participants. A typed version of the pre-discharge treatment plan will be sent to the outpatient clinician and the patient, and the accompanying letter will include the advice to discuss the plan and monitor its progress during every contact between them. The inpatient clinician is remunerated with CME credit points for each NODAPM intervention session and with a book voucher worth 50 € (once).

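### BPRS and HAM-D at T1–T3 are rated by an assessor accepted as unblinded without an adequate reason, although none of the information flows described requires that assessor to know the arm

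*Protocol article*

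**What the plan says.** In the protocol article, the Blinding section states: "The natural flow of the study will also prevent the research worker from being blinded". It gives no further reason. Its later remark that no bias is expected concerns the investigators and the person performing randomisation, so bias from the assessor is not discussed.

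On who assesses, the Overview says: "Assessment will be carried out by a research worker (different in person from the intervention worker". The Outcome measures section says: "Secondary outcomes will be provided by independent raters (research workers trained in study instrument use), clinicians, and patients". Table 1 assigns CAN-EU, CSSRI-EU, BPRS, HAM-D, MANSA and EQ-5D to the research worker at T0–T3. The clinician's GAF and CGI appear at T0 and T1 only.

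Three flows could reveal the arm:
- **Allocation reply.** The randomisation unit will "generate a patient code, and send it back to the study centre". The role that receives it is not named (Randomisation).
- **Needs ratings.** The intervention worker obtains the patient's "met and unmet needs in a basic plan (results of the CAN rating) from the research worker" (Pre-discharge intervention session). The three-month CAN ratings are used in the second session (Post-discharge intervention session).
- **Satisfaction with discharge planning.** Patient and clinician forms are used at T1 in the intervention group only (Clinician perspective; Patient perspective).

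One statement disturbs the separation of roles. The Randomisation section says that the intervention "will be carried out by a research worker with limited clinician involvement".

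**The concern.** Better clinical outcome is a stated secondary hypothesis. BPRS and HAM-D scores depend on the rater's judgement, and a rater who knows the arm may score more leniently in one group. Patients and treating clinicians cannot be masked, so the research worker is the only assessor who could be. The analysis fits a constant group effect over time (Statistical analysis). A rater shift that persisted across the follow-ups would be absorbed into that term and could not be told apart from a treatment effect.

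The plan has already taken the step that usually makes masking difficult, which is using separate people for assessment and intervention. It then gives masking up without showing what prevents it.

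**Working it through.** **Step 1. Which measures are exposed.**
- BPRS and HAM-D: rated by the research worker at T1, T2 and T3. Exposed.
- GAF and CGI: rated by unblinded clinicians, and not after T1. Masking the research worker would not change them.
- SCL-90-R: patient self-report. Not affected by the rater's judgement.
- CAN-EU: described as "an interviewer-administered instrument comprising 22 individual domains of need", but only the user rating is obtained, so it records the patient's view. MANSA and EQ-5D likewise report the patient's own state. The interviewer has less influence here.
- Hospital days and readmissions: each "will be assessed by a research worker at T1 – T3 via the German version" of the CSSRI-EU. The same person collects these primary outcomes, but counts leave less room for judgement.

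At 6 and 18 months, therefore, BPRS and HAM-D are the only observer-rated symptom measures.

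**Step 2. Does any described flow need the assessor to know the arm?**
- The allocation reply goes to the centre. It can go to the intervention worker, since nothing in the article gives the assessor a use for it.
- CAN results run from the assessor to the intervention worker. If they are passed on for every patient in both arms, the handover reveals nothing.
- The one-arm satisfaction forms are completed by patients and outpatient clinicians. The assessor need not handle them.
- The research worker informs patients during recruitment (Ethics), but the fax for randomisation is sent only after consent, so this step precedes allocation.
- Undue burden on a participant may be reported to the trial steering committee by either worker (Monitoring of flow and quality of data).

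None of them does. One channel cannot be rerouted: patients know their arm and may mention it during an interview.

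**Step 3. Illustration of size.** The plan gives no figure on rater bias, so there is none to reproduce. Inputs:
- 245 per group and 10% attrition at each measurement point (Sample size). This gives 245 × 0.9 = 220.5, taken as 220 at T1, and 245 × 0.9³ = 178.6, taken as 178 at T3.
- Rater bias b of 0.05, 0.10 or 0.20 SD. This is an assumption; the article gives no value.

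For one two-sided 5% comparison of two means with no true effect, SE = √(2/n) in SD units, and the rejection probability is Φ(b/SE − 1.96) + Φ(−b/SE − 1.96).

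| Assumed bias (SD) | T1, n = 220 | T3, n = 178 |
|---|---|---|
| 0 | 5.0% | 5.0% |
| 0.05 | 8.2% | 7.6% |
| 0.10 | 18.2% | 15.7% |
| 0.20 | 55.5% | 47.1% |

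Example for T1 and b = 0.10: SE = √(2/220) = 0.0953, b/SE = 1.05, and Φ(−0.91) + Φ(−3.01) = 0.181 + 0.001 = 0.182.

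To put this on the BPRS scale, the discharge-planning study cited in the Background (34.5 vs 41.0 points, effect size 0.57) implies an SD of (41.0 − 34.5)/0.57 = 11.4 points. The assumed range is then about 0.6 to 2.3 points.

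**The case against.** **Scope.** A reader might infer that every interview-based secondary outcome, or even the primary outcome, is compromised. The article does not support that. CAN is user-rated, the quality-of-life instruments carry the patient's view, the SCL-90-R is self-report, and admissions and days are counts. The point is confined to BPRS and HAM-D, which are secondary.

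**Feasibility.** Over three follow-ups and 18 months, the assessor asks about service contacts while intervention patients hold a typed treatment plan that is meant to come up at every outpatient contact. Some disclosure is inevitable. This stands: masking would be partial. It does not justify giving masking up altogether. A reader might also infer that rerouting needs no extra staff, but the article gives no staff numbers or capacity, and its two statements on who delivers the intervention do not agree.

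**Size.** It is tempting to say that rater bias could amount to a quarter or all of the effect the trial seeks. That reading fails. The 0.2 SD in the Sample size section belongs to a calculation for inpatient days, no BPRS target is set, and dividing an assumed bias by 0.2 only returns the assumption.

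**Wording.** A reader might see a contradiction between independent raters and unblinded raters. The word can fairly mean that they do not deliver the intervention, and the Blinding section is open about their status.

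**Article format.** Who receives a fax is an operational detail that an article may leave out. But the decision not to mask the assessor, and the only reason for it, are stated in the text.

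**Conclusion.** The concern holds for BPRS and HAM-D at T1–T3. The article accepts an unblinded assessor without an adequate reason, although assessor and intervention worker are already meant to be different people and no described flow requires the assessor to know the arm.

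The size of the resulting bias is unknown. The range of about 8–56% for the false-positive rate at T1 depends entirely on an assumed shift of 0.05–0.20 SD, a single comparison and the projected 220 per group. It shows sensitivity and is not an estimate.

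That masking can be improved with the two existing roles is probable but not stated. It depends on the roles being separate in practice. This is a worthwhile, low-cost improvement to secondary outcomes, and it does not challenge the primary analysis.

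**What to change.** First reconcile the Randomisation section with the Overview on who delivers the intervention. Then change the Blinding section so that the research worker is masked as far as possible:

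1. Send the allocation reply to the intervention worker only.
2. Pass the T0 and T1 CAN results of all patients, in both arms, to the intervention worker, who uses those needed.
3. Have the intervention-only satisfaction forms returned sealed or by post, handled neither by the assessor nor by the intervention worker whose sessions they rate. Having intervention workers collect ratings of their own sessions would add a bias of its own.
4. Ask patients not to disclose their arm to the assessor.
5. Rate BPRS and HAM-D before the CSSRI-EU service-use interview, where disclosure is most likely.
6. Record the rater's guess of allocation at T1, T2 and T3, and report it with the BPRS and HAM-D results.

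The cost is procedural wording, slightly more handover work because control patients' CAN results are passed on too, and a separate return route for the forms. Masking will remain partial. The recorded guesses would help readers judge how far it succeeded.
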